## Abstract

**Background:**

Total knee replacement (TKR) or total hip replacement (THR) are common and effective procedures in patients with osteoarthritis (OA) to restore physical function and reduce joint related pain. Patient education plays an important role in the treatment process aiming to develop necessary self-management skills to facilitate recovery and ensure long-term success. We have developed a mobile app (RECOVER-E) for iOS and Android smartphones which provides important information on the preoperative phase, surgery and recovery. The concomitant study will determine the efficacy of RECOVER-E on patients’ surgical outcomes.

**Methods/design:**

This study is a non-randomized, multi-centre (4 sites), double-arm, controlled trial with 1:1 assignment. 160 patients undergoing primary TKR or THR will be recruited from January until October 2019 in 4 German hospitals. Both groups will receive standard care. Additionally, the intervention group will use the app RECOVER-E. Measurements will be taken 4–6 weeks before surgery, on the day of admission to the hospital, on the first and 7th postoperative day and 3 months post-surgery. Primary outcome will be self-reported physical function measured on the activities of daily living (ADL) subscale of the Knee injury and Osteoarthritis Outcome Score (KOOS) and the Hip disability and Osteoarthritis Outcome Score (HOOS) for patients with knee and hip osteoarthritis, respectively.

Secondary outcomes include the subscales for pain, symptoms, function in sport and recreation and knee/hip-related quality of life of the HOOS and KOOS, preoperative anxiety, measured by the Hospital Anxiety and Depression Scale (HADS), as well as, pain at rest and pain during activity measured by a numerical rating scale (NRS). Primary endpoint is 3 months post-surgery.

**Discussion:**

Mobile Health (mHealth) has become increasingly important in patient-centred health care aiming to enhance patient involvement and self-management capabilities. To our knowledge this is the first study to investigate the effect of an evidence-based mobile app on patient reported outcomes after joint replacement. This study should provide evidence supporting the use of mHealth to facilitate recovery and open up new possibilities for patient care in joint replacement.

**Trial registration:**

DRKS Data Management retrospectively registered. DRKS-ID: DRKS00012744.

## Background

Osteoarthritis (OA) is worldwide one of the most common joint diseases that causes pain and functional disability and results in an increasing number of total hip or knee replacement procedures [1–4]. In Germany 162,524 hip replacement procedures and 178,479 knee replacement procedures were performed in 2016 due to hip or knee OA, respectively [5]. Due to the ageing of the population and an increase in obesity, the incidence and prevalence of these inflammatory joint diseases is growing and expectations to maintain a physically active lifestyle will most likely lead to a higher demand for surgery at a younger age [6, 7]. Thus, the requirement for total joint replacement is expected to increase steadily [6–8]. The main objective of joint replacement procedures is to restore greatest possible physical function and reduce pain. Especially in the elderly, these factors are considered as having an important impact on self-determination and social participation, and therefore, on quality of life [3, 9].

Total hip replacement (THR) and total knee replacement (TKR) are generally successful and lead to good clinical outcomes, but the procedure can be physically and psychologically challenging for patients [10, 11]. Same-day admissions in modern hospital practices and reduced length of hospital stay do not leave much time for patients to adjust to their situation [12]. Many people fail to recover optimally and continue to experience pain and functional problems [2, 10].

Preoperative education appears to have a positive effect on the patients’ postoperative coping abilities [13]. Pain disability, in particular, is largely influenced by how patients interpret and adapt to their pain [14]. Well-structured information about the surgery and the whole pathway of care supports patients’ understanding of their physical situation, relieves anxiety and empowers them to actively participate in their recovery [15]. Additionally, managing patients’ expectations prior to surgery is considered important for better physical function post-surgery and satisfaction with surgical outcomes [16, 17]. Long-term success of the joint replacement should be ensured by training the patients how to correctly perform daily activities and movements for gentle use of their artificial joint in daily life [18].

Recently, mobile apps have started to play an important role in monitoring and motivating patients to engage in their health [19]. Mobile Health (mHealth) apps aim to enhance patient involvement and self-management capabilities in patient-centred models of healthcare [20].

There are already a small number of apps that focus on patients undergoing hip or knee replacement [21–24]. Most of them are linked to specific hospitals or surgeons [25] and few of them are offered in German [26]. None of them evaluate the effectiveness on patient outcomes.

The project, pabee (“Patientenbegleiter für endoprothetische Eingriffe” – Patient Companion for Joint Replacement Surgery) wants to combine patient education with the mHealth approach in addition to designing a smartphone based, educative, intervention programme that accompanies patients from the preoperative phase, hospital admission, discharge and all the way until after rehabilitation.

The aim of the project, “pabee” is to develop an innovative mobile app for patients undergoing THR or TKR and to evaluate its efficacy on patient reported outcomes such as physical activity, pain, and quality of life.

The app contains evidence-based content on osteoarthritis and joint replacement procedures in the hip and knee. It aims to address patients’ training needs, support patients’ adherence and self-care competencies and to motivate them to actively participate throughout the entire treatment process.

This paper introduces the app RECOVER-E and details the study protocol of a double-armed controlled trial to determine the impact of the app on patient reported outcomes.

### Study hypothesis

The primary aim of the study is to test the hypothesis that patients undergoing TKR/THR using the app RECOVER-E attain better function in activities of daily living 3 months post-surgery when compared to patients undergoing surgery without using the app (control group).

Further hypotheses assume that patients using the app RECOVER-E experience significantly less symptoms, less pain, better function in sport and recreation, as well as a better knee/hip-related quality of life 3 months post-surgery when compared to the control group. Furthermore, we hypothesize less preoperative anxiety and postoperative pain in patients using the app RECOVER-E when compared to the control group.

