#### Information and education

Comprehensive text and video material aim to educate the patients and provide information on the disease, the artificial joint, the joint replacement procedure and everyday life after surgery. The preoperative phase focuses on information on the physiology of knee or hip, osteoarthritis, as well as, pain and pain management, but also gives a preview of daily activities with an artificial joint and support possibilities.

Patients will be prepared for the hospital stay and surgery by giving information on how to deal with allergies, general preparation for surgery, medication especially on pain and other pain management interventions [27].

The intra- and postoperative phase contains information on the hospital stay and the procedure itself, complications and how to prevent them, wound care, bowel function and body hygiene.

In the rehabilitative phase and home environment, users are encouraged to take part in their pain management, as well as, in their wound and scar care by frequent monitoring with the tools provided in the app. They are given information on rehabilitation, sports, sleep, sexual activity and returning to work post surgery. Users are offered 8 video clips with short and simple exercises to train muscles and increase flexibility in the legs for either knee or hip surgery (e.g. seated leg extension, elevation of legs while sitting) [31].

RECOVER-E proposes a certain number of repetitions and sets per exercise, which gradually increase after hospital discharge and after rehabilitation to keep training motivationally attractive. However, users are requested to first consult their physiotherapist to individually decide on the appropriate exercise intensity at any stage.

Since emotional well-being is closely and positively linked to the experience of control over one’s own recovery process, RECOVER-E provides important information on symptoms and self-management in the immediate postoperative phase. The app also motivates users to ask family and friends for support in order to bridge difficult and frustrating time periods during the first weeks after surgery [32].

Overall RECOVER-E’s education abilities aim to prepare users for an everyday, joint-sensitive life after their joint replacement surgery.

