#### Communication

The app comprises an interface for the clinical care teams. This will be used by participating hospitals to provide customized information on centre-specific procedures, teams and other information, the hospitals want to share regarding the organisation of the surgery and hospital stay. Additionally, health data provided by users in their app-based monitoring can be transferred to a specific web site accessible only by clinicians of the participating wards. Users have to give individual permission to transfer information from the pre-hospital and hospital phase only. That information can support the problem-centred conversations with nurses and doctors and give insight on pain- and function-based problems during the preparation phase of the surgery and after the operation.

Another feature to facilitate communication after discharge is an automatic message service to inform the users’ orthopaedist in case of complications after discharge: back at home users are instructed to continue self-assessment of pain, function and to observe their wound. If thresholds are exceeded, the app offers to inform the orthopaedist via fax. Users are free to decide on each individual occasion whether or not that information should be sent to their orthopaedist. They are told to visit a doctor immediately in case they observe a further decline in their health.

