### Outcomes

Data presented in Table 1 will be measured in the study.

**Table 1 Tab1:** Study measures to be collected

Measure	Instrument	t_0_	t_1_	t_2_	t_3_	t_4_
Primary outcome measure						
Activities of daily living (ADL)	KOOS/HOOS subscale ADL (self-reported)	x				x
Secondary outcome measures						
Pain, symptoms, Sport & Rec and quality of life	KOOS/HOOS subscales pain, symptoms, Sport & Rec and quality of life (self-reported)	x				x
Pain at rest	NRS (self-reported)	x	x	x	x	x
Pain during activity	NRS (self-reported)	x	x	x	x	x
Preoperative anxiety and depression	HADS (self-reported)	x	x			
Other measures						
Usage metrics	number of user sessions, length of time participants interact with the app, content they engage with, frequency of recording self-monitoring parameters, number of awards	continuous recording				
Physical activity	IPAQ (self-reported)	x				
Social support	questionnaire (self-reported)					x
Physician visits post-surgery	questionnaire (self-reported)					x
Use of pain medication	medical record, questionnaire (self-reported)		x	x	x	x
Sex, age	medical record				x	
BMI (size, weight)	medical record				x	
Operated joint	medical record				x	
OPS, ICD	medical record				x	
Comorbidities	medical record				x	
Duration of hospital stay	medical record				x	
Type and duration of planned and performed rehabilitation programme	medical record, questionnaire (self-reported)				x	x
Complications post-surgery	medical record, questionnaire (self-reported)			x	x	x
Structural data of hospitals						
- Number of beds - Number of joint replacement surgeries performed over the past 12 months - Number of nurses in the orthopaedic departments: nurses, nursing assistants, Pain Nurses, full-time equivalent - Number of physicians in the orthopaedic departments: total number, number of orthopaedic specialists, full-time equivalent - Process quality management data for the care of patients with THR/TKR (documentation forms and guidelines, interprofessional standard operating procedures for analgesic therapy, pain management guidelines, other pain therapy guidelines, standard operating procedures for patients with THR/TKR, special contracts with other facilities and mandatory health insurance companies for structured patient care) - Regular cooperation with institutions of inpatient or outpatient rehabilitation						

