*KOOS* knee injury and osteoarthritis outcome score, *HOOS* hip disability and osteoarthritis outcome score, *NRS* numerical rating scale, *HADS* Hospital Anxiety and Depression Scale, *IPAQ* International Physical Activity Questionnaire, *BMI* body mass index, *OPS* “Operationen- und Prozedurenschlüssel” (= key for surgery procedures), *ICD* International Statistical Classification of Diseases and Related Health Problems, *THR* Total hip replacement, *TKR* Total knee replacement

The primary outcome measure of the study will be the activities of daily living (ADL) subscale of the Knee injury and Osteoarthritis Outcome Score (KOOS) [35] and the Hip disability and Osteoarthritis Outcome Score (HOOS) [36]. The extensive subscale comprises a variety of daily activities (17 items). A 5-point Likert-scale is used and converted into a normalized 100-point score with zero indicating the worst possible function [35–39]. KOOS and HOOS were chosen, because both provide measures of the same subscales, but adapted for knee and hip, respectively. They have been shown to have good reliability and validity in patients undergoing joint replacement [35, 40].

Secondary outcomes are the subscales for pain, symptoms, function in sport and recreation and knee/hip-related quality of life of the HOOS and KOOS, the preoperative anxiety, measured by the Hospital Anxiety and Depression Scale (HADS) [41, 42] as well as their currently experienced pain at rest and pain during activity measured by an 11 point numerical rating scale (NRS; 0 “no pain” – 10 “maximum pain”).

Other measures collected by self-administered questionnaires and further information registered by the medical record include physical activity measured by the International Physical Activity Questionnaire (IPAQ) [43], social support at recovery, post-surgical physician visits, use of pain medication, sex, age, BMI (body mass index; size, weight), operated joint, OPS (“Operationen- und Prozedurenschlüssel” – key for surgery procedures), ICD (International Statistical Classification of Diseases and Related Health Problems), comorbidities, duration of hospital stay in days, type and duration of planned and performed rehabilitation programme and complications post-surgery.

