### Data analysis

Baseline data, clinical and demographic characteristics will be presented to show the baseline comparability of the intervention group and the control group. The analysis will include all patients following the intention-to-treat principle, drop-out and loss to follow-up will be described. Data will be checked for completeness and normality. The treatment effect will be evaluated by the change in ADL using between group analyses, such as independent t-test and ANCOVA to adjust for demographic factors such as age, sex, BMI (body mass index), baseline pain, anxiety, joint, comorbidities, physical activity, pain medication, type and duration of rehabilitation and social support on change in outcomes. For comparison within groups paired t-tests will be conducted. Within the intervention group the relationship between usage metrics and patient reported outcomes will be analysed using linear regression analyses.

All statistical analyses will be performed using IBM SPSS Statistics for Windows, version 24 (IBM Corp., Armonk, N.Y., USA).

Results of the study will be presented at conferences and placed in journals.

The controlled trial will be accompanied by multi-perspective qualitative research approaches to understand user decisions and long-term user engagement of the intervention. These studies will be reported elsewhere.

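### Pain medication has no pre-intervention value and appears only as an adjustment factor, so a difference in pain scores could partly reflect different analgesic use

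*Protocol article*

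**What the plan says.** All references are to the protocol article.

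- **Study hypothesis.** Lower postoperative pain is a claimed benefit: "Furthermore, we hypothesize less preoperative anxiety and postoperative pain in patients using the app RECOVER-E when compared to the control group".
- **Outcomes.** The secondary outcomes include "currently experienced pain at rest and pain during activity measured by an 11 point numerical rating scale". Table 1 marks both NRS items at every time point, t0 to t4, and the KOOS/HOOS pain subscale at t0 and t4.
- **Outcomes, Table 1.** The row "Use of pain medication" stands under other measures. Its sources are the medical record and a questionnaire. It is marked at t1, t2, t3 and t4, and its t0 cell is empty. The text below the table lists it with background variables: "social support at recovery, post-surgical physician visits, use of pain medication, sex, age, BMI".
- **Intervention group.** Participants get the access link immediately after the t0 data collection, 4 to 6 weeks before surgery.
- **Information and education.** Preparation for the hospital stay covers "general preparation for surgery, medication especially on pain and other pain management interventions".
- **Communication.** With the user's permission, app data from the pre-hospital and hospital phases can go to ward clinicians, where they can "give insight on pain- and function-based problems during the preparation phase of the surgery and after the operation".
- **Data analysis.** Pain medication appears once, in the ANCOVA adjustment list: "baseline pain, anxiety, joint, comorbidities, physical activity, pain medication, type and duration of rehabilitation and social support on change in outcomes".
- **Participants and recruitment; Discussion.** Controls come from January to May 2019 and app users from June to October 2019. The Discussion names the lack of randomisation as a major limitation and answers it with a full analysis of group comparability.

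**The concern.** Analgesics act directly on the pain score, and this intervention gives patients information about them. Two things follow from the schedule and the stated analysis.

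First, baseline pain in each cohort is scored under unknown analgesia. With sequential cohorts the baseline comparison carries much of the burden that randomisation would otherwise carry. Two cohorts with equal NRS at t0 may still differ in how much medication lies behind that score. Baseline pain is also an ANCOVA covariate, so the gap carries into the adjusted analysis.

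Second, pain medication enters the stated analysis only as something to adjust for. Without a t0 value, the covariate has to come from t1 or later, after app users have had access. Adjusting for it then conditions on a variable that the app may have changed.

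At stake is how a pain result is read. Lower NRS with more medication, lower NRS with the same medication, and equal NRS with less medication are different findings. A reader needs both quantities by arm to tell them apart.

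**Working it through.** The plan gives no figure on analgesic use, so none can be reproduced. The main check sets the sections side by side; a short illustration of size follows.

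**Step 1: timing.**

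| Item | t0 | t1 | t2 | t3 | t4 |
|---|---|---|---|---|---|
| NRS pain, rest and activity | x | x | x | x | x |
| KOOS/HOOS pain | x | | | | x |
| Pain medication | | x | x | x | x |
| App access (intervention group) | starts right after t0 | yes | yes | yes | yes |

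The only time point before app access is t0, and it is the only one without a medication entry. The t1 value cannot stand in for it, because app users will by then have had access for the weeks between t0 and admission.

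**Step 2: role in the analysis.** The covariate sentence is written for change in ADL and ends by referring to change in outcomes generally. Whichever outcome is meant, Step 1 leaves only t1 to t4 as sources for the medication covariate. If the app changes medication and medication changes pain or function, the adjusted contrast removes that part of the app's effect. If unmeasured factors influence both medication and outcome, adjustment can also introduce bias, in either direction. Without adjustment and without a by-arm display, the part of an NRS difference that runs through medication is not visible.

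**Step 3: comparability.** The comparability analysis promised in the Discussion can use only what is measured before the intervention, or what the intervention cannot change. On the printed schedule, analgesic use meets neither condition.

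**Step 4: size, as an illustration.** Only the sample size comes from the documents: 58 knee + 58 hip = 116 analysable patients, which at 1:1 is 58 per arm with the joints pooled and 29 per arm within one joint. The other inputs are assumptions:

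- 10 to 20 percentage points more app patients take additional analgesics;
- each of them gains 1 to 2 NRS points;
- the SD of NRS is 2.

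Shift in mean NRS = difference in use × gain per user:
- low: 0.10 × 1 = 0.1 points
- high: 0.20 × 2 = 0.4 points

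Standard error = SD × √(2/n per arm):
- pooled: 2 × √(2/58) = 0.37, so the shift is 0.1/0.37 = 0.3 to 0.4/0.37 = 1.1 SE
- within one joint: 2 × √(2/29) = 0.53, so the shift is 0.1/0.53 = 0.2 to 0.4/0.53 = 0.8 SE

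On these inputs, medication alone would not reach 1.96 SE, but it could contribute part of an observed difference.

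**The case against.** The strongest reply is that the plan does not ignore analgesia. Medication is recorded at t1 to t4, which covers every postoperative NRS assessment, and it is a named ANCOVA factor. This stands. A reader might infer that the trial could never separate better recovery from heavier analgesia, or that a lower score would simply be more medication. The documents do not support that, because the data for a by-arm display will exist.

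A reader might also infer that analgesic use is never to be compared between arms. The documents show only that this article states no such comparison. The article is condensed and names a between-group test only for change in ADL; a fuller plan may tabulate the other measures.

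Next, pain relief through better-used analgesia may be an intended effect. Pain management is deliberate app content and was a literature-review topic in its development. The hypothesis is less pain, not less pain at equal analgesia. This stands too. It rules out a condition that less pain may be concluded only when analgesic use is not higher in the app arm: that would be a different estimand, and nothing in the documents calls for it.

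The contrast between arms should also not be overdrawn. Controls receive verbal information on perioperative treatment, some clinics add folders, and nothing says analgesia is left out. Transfer of app data to clinicians needs the user's permission.

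Finally, Table 1 lists no medical-record item at t0, and nothing shows that preoperative analgesic use is documented for controls already enrolled. This limits the remedy for those patients, but does not remove the gap.

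None of these replies supplies a pre-intervention value or makes a t1 to t4 covariate safe.

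**Conclusion.** The point holds in a limited form. On the printed schedule there is no analgesic value before app access in either cohort, so baseline pain is scored under unknown medication and the comparability check has a gap. The only stated use of pain medication is as a covariate, which must then be post-exposure to an app that informs on pain medication. A difference in NRS could therefore partly reflect different analgesic use.

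The size is unknown from the documents. Under the assumed inputs it is 0.1 to 0.4 NRS points, at most about 1.1 SE, so this is not shown to be enough to produce a false pain claim by itself. For pain the matter concerns secondary outcomes. The primary ADL result is touched only through the choice of medication covariate in its adjusted analysis, and that effect was not sized. It is an inexpensive improvement, not a fatal defect.

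**What to change.** 1. **Table 1:** add use of pain medication at t0 and include it in the baseline comparability table. Use the same source in both cohorts, for example the medical record where it documents preoperative use. State how many already-enrolled controls lack the value.
2. **Data analysis, reporting:** report analgesic use at t1 to t4 by arm, beside NRS at the same time points, so that the two are interpreted together. No condition on the pain conclusion is needed.
3. **Data analysis, covariates:** specify the t0 value, not the t1 to t4 values, as the medication covariate for the treatment effect.

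Cost: one extra baseline item and one extra table from data already scheduled. At submission in May 2019 only controls were being recruited and the app was still in final testing, so the item could be added for the whole app cohort. The downside is that the t0 value may be incomplete for controls already enrolled.
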